#### Primary outcome

The Western Ontario and McMaster Universities Osteoarthritis Index (WOMAC) as an objective indicator of efficacy is the primary efficacy endpoint of the study; this is a widely used, proprietary set of standardized questionnaires used by health professionals to evaluate the condition of patients with osteoarthritis of the knee and hip, including pain, stiffness, and physical functioning of the joints [25]. The WOMAC measures 5 items for pain (score range 0–20), 2 for stiffness (score range 0–8) and 17 for functional limitation (score range 0–68) to assess the severity of arthritis and the therapeutic effect according to the patients’ symptoms and signs. It can fully reflect the basic situation of osteoarthritis [26]. The primary outcome is improvement in total WOMAC scores, which will be measured during the assessment visits (baseline and 1-week and 2-week follow up).

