### Sample size estimation

Our study was designed as a non-inferiority trial and sample size calculations are based on the primary outcome measurement. First, the minimal clinically important difference in WOMAC scales in KOA is estimated from previous studies [28] as 15.50 points. Second, we assume that based on previous literature [29], the square deviation of the WOMAC score is 318.88. For power of 80% and an alpha value of 2.5% (two-tailed), the sample size is calculated using the following formula:$$ n=\frac{\frac{4}{3}{\left({u}_{\upalpha}+{u}_{\beta}\right)}^2{\upsigma}^2}{{\left(\varDelta -\updelta \right)}^2}\ \left({u}_{\upalpha}=1.6449,\kern0.5em {u}_{\beta }=1.2816\right) $$

Thus, we obtained the sample size of 1600 patients for this trial; allowing for a conservative 20% dropout rate, the total sample size was set at 2000 patients (1500 in the Tong-luo Qu-tong plaster group).

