### Randomization

This study is designed as a randomized, double-blind, parallel positive drug controlled, multicenter clinical trial. A total of 2000 eligible participants will be randomized (3:1) using a stratified-block randomization method based on the disease and the center to two treatment groups: the experimental group (Tong-luo Qu-tong group) and the control group (Qi-zheng Xiaotong group). A number of previous clinical studies also had adopted unequal allocation-ratio designs, which allows the minimization of potentially unethical exposure of patients to a placebo [30–32]. However, our study lacked a placebo group, which is different from previous studies. Based on the above, we drew up an appropriate unequal allocation ratio. All eligible patients were assigned in a 3:1 ratio (Tong-luo Qu-tong plaster group: Qi-zheng Xiao-tong plaster group) by a stratified-block randomization method; the study design ensured a greater number of patients undergoing Tong-luo Qu-tong plaster exposure by employing an unequal allocation ratio. This provided better safety assessment and greater exposure for testing the efficacy of Tong-luo Qu-tong plaster in this randomized controlled clinical trial, to generate good evidence to answer the trial research question. SAS statistical software 9.2 (SAS Institute, Cary, NC, USA) will be used to generate a randomization scheme based on the PROC PLAN function, which will be used to link the patient to a treatment arm and will specify a unique medication number for the first package of study drug to be dispensed to the patient.

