### Statistical analysis

The statisticians and the main researchers are responsible for the statistical analysis plan. We will analyze all data with SAS 9.2 statistical software. Data sets including the full analysis set (FAS), per-protocol set (PPS) and safety set (SS), will be analyzed in terms of actual subjects, shedding cases, excluding cases, demographic and characteristics of cases, and efficacy and safety analyses will be conducted according to the intention-to-treat (ITT) principle.

Categorical data presented as frequency tables or percentages and continuous data presented as mean ± standard deviation, median, superior and inferior quartiles, minimum value and maximum value will be used to describe the characteristics of patients in both groups. The primary outcome will be compared in the two groups; categorical data will be analyzed by chi-squared test or Fisher’s exact test, and continuous data with a normal distribution will be analyzed by the *t* test or variance testing. If the data are not normally distributed or do not satisfy homogeneity of variance, they will be analyzed using the Wilcoxon rank sum test or Wilcoxon symbols test to compare the two treatment arms. A two-sided *P* value ≤0.05 or ≤0.01 will be considered statistically significant.

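### The primary test is chosen by distribution checks and read by a P value for difference, where a non-inferiority comparison needs one fixed, baseline- and centre-adjusted mean difference with a 95% interval

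*Protocol article*

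**What the plan says.** - **Design** (Sample size estimation): "Our study was designed as a non-inferiority trial and sample size calculations are based on the primary outcome measurement". The only WOMAC difference printed there is 15.50 points, described as a minimal clinically important difference. The variance is 318.88.
- **Endpoint** (Primary outcome): "The primary outcome is improvement in total WOMAC scores, which will be measured during the assessment visits (baseline and 1-week and 2-week follow up").
- **Test if the data look normal** (Statistical analysis): "continuous data with a normal distribution will be analyzed by the *t* test or variance testing".
- **Test otherwise**: "If the data are not normally distributed or do not satisfy homogeneity of variance, they will be analyzed using the Wilcoxon rank sum test". The same sentence then offers a second option for this case: "or Wilcoxon symbols test to compare the two treatment arms".
- **Decision rule**: "A two-sided *P* value ≤0.05 or ≤0.01 will be considered statistically significant".
- **Randomization**: 3:1, "using a stratified-block randomization method based on the disease and the center". Eleven hospitals take part.

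The Statistical analysis section names no covariate, centre term, confidence interval or margin for the primary comparison.

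**The concern.** Non-inferiority is shown by placing an interval for the treatment difference against a margin on the same scale. The published rule does something else, in four respects.

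1. The test, and with it the quantity being estimated, is settled only after the distributions have been inspected.
2. One of the possible outcomes is a rank-sum P value against no difference. A non-significant result there does not show non-inferiority, and the P value alone carries no mean difference in WOMAC points.
3. The Wilcoxon symbols test is most plausibly the signed-rank test. That is a paired test and cannot compare two independent arms, which is the use the sentence gives it.
4. Rank-sum is offered as the answer to unequal variances. Its null variance assumes identical distributions, so it does not fully protect against unequal spread, least of all with unequal group sizes.

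In addition, baseline WOMAC is collected and centre stratifies randomisation, but the stated comparison uses neither as an adjustment. At stake are a primary estimand that can shift with the data, a result that may not be readable against the margin, and some lost precision.

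**Working it through.** **Inputs from the article.** Variance 318.88, so SD = √318.88 = 17.86. Before dropout there are 1600 patients at 3:1, that is 1200 and 400; 1600/0.8 = 2000 reproduces the dropout step. The 1600 is used here only as the number analysed; how it was derived is a separate matter.

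**Assumptions, not in the article.** Baseline to week-2 correlation r of 0.3 to 0.7; ratios of control SD to experimental SD of 0.8, 1, 1.25 and 1.5; 5% thresholds for the normality and variance checks, since the article names neither the tests nor their levels.

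**Step 1: which test would be used?** Simulated at 1200:400 with equal distributions in both arms, using Shapiro-Wilk and Levene checks:
- truly normal data: about 12% of trials are sent to rank-sum (3000 runs);
- integer scores with skewness 0.5: essentially 100% are sent to rank-sum (3000 runs).

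At these group sizes the sampling distribution of a mean difference is close to normal in either case, so the check guards against nothing that matters for a comparison of means.

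**Step 2: error of the whole two-stage rule.** Equal means, two-sided 5%, 1200:400. Ranges are over separate simulations of normal data, except that the equal-SD row also includes the skewed scores.

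| Control SD / experimental SD | Two-stage error |
|---|---|
| 0.8 | about 4% |
| 1 | about 5% |
| 1.25 | about 6-7% |
| 1.5 | about 7-9% |

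With unequal SDs the variance check sent virtually every trial to rank-sum, so the last two rows are in effect the error of rank-sum itself. With equal SDs, switching alone caused no inflation.

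**Step 3: precision.** The unadjusted SE for the week-2 score is 17.86 × √(1/1200 + 1/400) = 1.031, and the 95% half-width is 1.96 × 1.031 = 2.02 points. Relative to the score variance, a change score has variance 2(1 − r) and ANCOVA on baseline has 1 − r². Their ratio is (1 − r²)/[2(1 − r)] = (1 + r)/2.

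| r | Change: SE (half-width) | ANCOVA: SE (half-width) | Variance reduction vs change |
|---|---|---|---|
| 0.3 | 1.220 (2.39) | 0.983 (1.93) | 35% |
| 0.5 | 1.031 (2.02) | 0.893 (1.75) | 25% |
| 0.7 | 0.799 (1.57) | 0.736 (1.44) | 15% |

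If 5-10% of residual variance lies between centres (assumed), adding centre lowers the ANCOVA SE at r = 0.5 to about 0.85-0.87. In simulated stratified 3:1 allocation over 11 centres, the ANCOVA's error was 3.7-6.2% over nine settings of 1000 runs each, consistent with 5%.

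**Step 4: does the precision matter for the verdict?** Suppose 15.5 points is the margin and the true difference is zero. Power is Φ(15.5/1.031 − 1.96) = Φ(13.07) without adjustment and Φ(15.5/0.893 − 1.96) = Φ(15.40) with it. Both are essentially 100%.

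**The case against.** The strongest reply is that covariates, robust standard errors and intervals belong in the statistical analysis plan, which the article mentions and which is not shown. That holds for the bare absence of covariates, which would not be a finding alone. It does not cover the switching rule, the signed-rank test or the P-value criterion. The article states these itself, and an analysis plan could cure them only by overriding the published text.

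Other parts of the defence also stand:
- A reader might infer that baseline is ignored. The endpoint is "improvement", most naturally change from baseline, so baseline is subtracted although not adjusted for. An unadjusted comparison of change is valid under randomisation; ANCOVA is simply more efficient. Variance testing may mean analysis of variance, which could carry a centre factor, but none is named.
- A reader might infer that no result could be set against a margin. The t-test route can yield a mean-difference interval, and rank-sum can be accompanied by a Hodges-Lehmann shift interval under a shift assumption. The article plans neither, and a pure shift does not hold when variances differ.
- A reader might infer that a pooled t test with unequal variances would badly inflate error under 3:1. The plan sends such data to rank-sum, so that error does not describe this trial. The inflation in the table is smaller and reverses when the control SD is the smaller one. The article gives no ground for either direction.
- A reader might infer that rank-sum is certain to be used. That depends on the shape of the data and on unnamed checks.

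**Conclusion.** The concern holds for the rule as published. The primary test depends on the data, a paired test is listed for independent arms, and the criterion is a P value for difference in a non-inferiority trial. This should be corrected, but it is not fatal: the data needed for a sound analysis are already being collected.

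The error consequence is moderate and conditional: about 6-7% or 7-9% against a nominal 5% if the control SD is 1.25 or 1.5 times the experimental SD, about 5% if equal, and below 5% if smaller. Adjustment would cut variance by 35% to 15% relative to a change score for r from 0.3 to 0.7. The SD ratios and r are assumptions.

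A reader might also infer that adjustment rescues the trial's power. The documents do not support that. The only difference printed is 15.50 points, against which power is essentially complete either way; a material gain would need a much smaller margin, which the article does not state. The case for the change rests on a fixed estimand and an interval on the margin's scale, with precision as a further benefit.

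**What to change.** Make the primary analysis one prespecified ANCOVA of week-2 total WOMAC (or its change from baseline) on treatment, baseline total WOMAC and centre. Use heteroscedasticity-robust standard errors. Report the adjusted mean difference with a two-sided 95% CI and compare that interval with the stated non-inferiority margin, whatever the distribution checks show.

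Delete the normality and equal-variance switch for the primary outcome, and delete the signed-rank test as a between-arm comparison. Keep rank-sum as a sensitivity analysis only. Replace the P-value criterion for the primary outcome with the interval rule.

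The cost is revised wording in the protocol and analysis plan and one linear model in the SAS software already planned. No new data, visits or patients are needed, provided that the change is made before unblinding.

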## Methods and designs

### Trial design

This will be a randomized, double-blind, parallel positive controlled, multicenter clinical trial; a non-inferiority trial design was adopted. With the unceasing development of medical technology, there are increasing numbers of positive drugs with the exact curative effect in clinical treatments. Once a treatment has been established as effective, it would be unethical to undertake placebo-controlled trials [17], which has led to more widespread application of clinical non-inferiority trials over recent decades [18, 19]. A non-inferiority trial design could be a better alternative to indirectly show the efficacy of a new treatment [20].

Each participant will sign an informed consent form (ICF) before the research is performed. A total of 11 medical institutions are involved in the study; subjects will be enrolled at eleven hospitals, including Longhua Hospital Affiliated to Shanghai University of TCM, The first Affiliated hospital of Guangzhou University of TCM, Zhengzhou Central Hospital, Suzhou Hospital of TCM, Luoyang Orthopaedics-Traumatological Hospital, Xiangyang First People’s Hospital, Liaoning Hospital of TCM, The Second Hospital of Nanjing Medical University, The Fourth Central Hospital of Tianjing, Changchun University of TCM and Shandong University of TCM. Longhua Hospital Affiliated to Shanghai University of TCM takes charge of the total clinical scheme design. The study protocol has been approved by the ethics committee of Shanghai University of TCM on the use of human subjects for research (approval number 2016LCSY097); each participating center has conducted ethical filing and has ethical approval from the main central hospital.

The study phases are shown in Fig. 1. A total of 2000 patients with KOA will be recruited and randomly allocated into the experimental group (*n* = 1500) or the control group (*n* = 500); each patient will undergo a 2-week treatment with herbal patches for one session per day. A flow chart of trial participation is provided in Fig. 2. Efficacy and safety data will be collected throughout the whole study.

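### The trial is declared and sized as non-inferiority, but the analysis stated for the primary outcome is a two-sided test of difference with no margin

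*Protocol article*

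**What the plan says.** The design is stated plainly. Under Trial design: "multicenter clinical trial; a non-inferiority trial design was adopted". Under Sample size estimation: "Our study was designed as a non-inferiority trial and sample size calculations are based on the primary outcome measurement". The comparator is an active plaster.

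Under Primary outcome: "The primary outcome is improvement in total WOMAC scores", "which will be measured during the assessment visits (baseline and 1-week and 2-week follow up").

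The Statistical analysis section says that the primary outcome will be compared between the two groups. Continuous data are to be analysed by t test or variance testing, or by a Wilcoxon test if normality or equal variance fails. The criterion is that a two-sided P "value ≤0.05 or ≤0.01 will be considered statistically significant".

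The sample-size section states its error rates thus: "For power of 80% and an alpha value of 2.5% (two-tailed), the sample size is calculated using the following formula". The formula printed beneath it uses u_alpha = 1.6449 and u_beta = 1.2816 and divides by (Delta − delta) squared. Neither Delta nor delta is defined or given a value. The only WOMAC difference quoted is a minimal clinically important difference, given "as 15.50 points". It is not called a margin and does not reappear in the analysis.

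**The concern.** A t test or Wilcoxon test with a two-sided P value tests the null hypothesis that the arms are equal. A non-inferiority trial has to reject a different null, namely that the experimental plaster is worse than control by at least the margin. That is normally done by comparing a confidence limit with the margin. The test and criterion printed for the primary outcome therefore belong to a different hypothesis from the one the trial was set up to answer.

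The result most likely to matter in a non-inferiority trial is a small difference in either direction, and the stated rule cannot interpret it. Failure to reject equality does not show that a deficit of the size of the margin has been excluded. With some 1600 evaluable patients, a deficit small enough to be acceptable could also be statistically significant. Two alternative thresholds, with no rule for choosing between them, leave the criterion itself open.

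**Working it through.** **1. Can the margin be recovered from the sample size?**

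Inputs from Sample size estimation and Randomization: variance 318.88 (SD 17.86), u_alpha 1.6449, u_beta 1.2816, 3:1 allocation, 1600 before dropout. Assumption: Delta − delta = 15.50, that is, the clinically important difference is the margin and the true difference is zero.

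- n = (4/3)(1.6449 + 1.2816)² × 318.88 / 15.50² = (4/3) × 8.564 × 318.88 / 240.25 = 15.2. With 3:1 allocation the factor 4/3 makes this the control-arm size, so 16 controls and 64 in total, not 1600.
- With quantiles for one-sided 2.5% and 80% power (1.96, 0.8416), n = 13.9, so 14 controls and 56 in total.
- Solving backwards for 400 controls (1600 in total): Delta − delta = √[(4/3) × 8.564 × 318.88 / 400] = 3.02 with the printed quantiles, or 2.89 with 1.96 and 0.8416. If the formula's n is itself 1600, the value is 1.51.
- The dropout step does reproduce: 1600 / 0.8 = 2000.

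The figure of 1600 is not reproduced from 15.50, and the margin could be read as about 3 or as 15.50.

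**2. Precision of the comparison**

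Assume 1200 and 400 evaluable patients and variance 318.88.

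- SE = √[318.88 × (1/1200 + 1/400)] = √1.063 = 1.031 points.
- Half-width of the two-sided 95% CI = 1.96 × 1.031 = 2.02 points.

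**3. What the difference test does when the plaster is truly 3.0 points worse**

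- Probability of P ≤ 0.05: Φ(3/1.031 − 1.96) = Φ(0.95) = 0.829, so non-significant in about 17% of trials.
- Probability of P ≤ 0.01: Φ(3/1.031 − 2.576) = Φ(0.33) = 0.631, so non-significant in about 37%.

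**4. Reading this under each candidate margin**

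| Assumed margin | A plaster truly worse by 3.0 points is | What the difference test shows |
|---|---|---|
| about 3 points | at the non-inferiority boundary | non-significant in about 17% (0.05) or 37% (0.01) |
| 15.50 points | clearly non-inferior | significant at 0.05 in about 83% |

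With a 15.50-point margin, a deficit equal to the margin lies 15.50/1.031 ≈ 15 standard errors from zero. A non-significant result would then have essentially zero probability.

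**5. The error rates side by side**

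| Place | Level | One-tail equivalent |
|---|---|---|
| Sample size text | 2.5%, two-tailed | 1.25% |
| Sample size formula | u_alpha = 1.6449 | 5% |
| Analysis, first threshold | 0.05, two-sided | 2.5% |
| Analysis, second threshold | 0.01, two-sided | 0.5% |

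No two agree. The usual one-sided 2.5% for non-inferiority matches only the first analysis threshold.

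**The case against.** The strongest defence is that this is a condensed article that refers to a separate statistical analysis plan, and that a confidence-interval rule and the choice of decisive visit are commonly left to that plan. The analysis paragraph also reads as generic, since it covers chi-squared and Fisher tests although total WOMAC is continuous. This carries weight against any complaint of mere omission. It does not remove the conflict: the article goes beyond silence and names a test and a significance criterion for the primary outcome, and these address equality. A margin-based rule in the unseen plan would contradict the published text, which would still need correcting.

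Three stronger readings are tempting and are not supported.

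- A reader might infer that the rule can never establish non-inferiority. That is too absolute: a significant result favouring the experimental plaster shows superiority and so implies non-inferiority.
- A reader might infer that the sponsor intends to read a non-significant P as non-inferiority. No section says so; the 17% and 37% describe what would follow if someone did.
- A reader might infer from the two post-baseline visits that success at either would count, with inflated error. The article lists the visits but states no such rule, so no multiplicity error can be charged to it.

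It is also fair to object that the 3-point margin is back-solved from a sample size the printed inputs do not reproduce, while 15.50 is the article's own figure. For that reason both are shown. Nor is 2.5% the article's established error rate. It is the conventional benchmark; 17% also exceeds the 5% implied by the printed quantile.

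**Conclusion.** The point holds as a contradiction between the declared design and the stated primary analysis. Unless the experimental plaster is significantly better, the printed criterion cannot show non-inferiority. The choice between 0.05 and 0.01 is unresolved, and the alpha does not agree with the sizing section.

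The numerical consequence is conditional. With a margin of about 3 points, reading non-significance as non-inferiority would err in roughly 17% of trials at 0.05 and 37% at 0.01 for a plaster worse by 3 points, far above 2.5%. With a margin of 15.50 points that error is essentially zero, and the difficulty reverses: acceptable deficits would often be significant. Both statements assume variance 318.88, 1200:400 evaluable patients and a normal approximation. The mismatch itself rests on none of these assumptions. It must be fixed, because the stated rule does not test the stated question.

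**What to change.** Before unblinding:

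1. State the margin Delta as a number of WOMAC points and justify it. Reconcile it with the 15.50 points and with the undefined Delta and delta in the sample-size formula. The choice affects power: at a true difference of zero, one-sided 2.5% and 1200:400 evaluable, power is about 49% for a margin of 2 points, 83% for 3 and 99.8% for 5.
2. Replace the primary criterion with: non-inferiority is concluded if the upper limit of the two-sided 95% confidence interval for the difference (experimental minus control) in mean WOMAC total at week 2, the end of treatment, lies below Delta. Higher scores are worse, so a positive difference is a deficit.
3. Delete the 0.01 alternative. Reconcile the single remaining alpha with the sizing section, where the text and the quantile 1.6449 disagree.
4. If superiority is of interest, read it from the same interval once non-inferiority is met. Adjustment for baseline WOMAC is optional and would gain precision at no cost.

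The analysis change is one of wording and needs no new measurements. Whether the planned size suffices depends on the margin chosen in step 1. The article was published in June 2019 and gives December 2020 for completion of recruitment, so the planned timetable left room for the change.
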